
### Intervention

2.5.

All participants who meet the inclusion criteria and consent to participate will receive a psychological intervention based on the “Unified Protocol for the Transdiagnostic Treatment of Emotional Disorders” by Barlow et al. (2018). The UP is a 8 module treatment designed to be applied originally in 12 to 16 individual sessions (Farchione et al., 2021). As the UP developers mentioned, clinicians can be flexible in the number of sessions that are needed to complete each module and also in the order in which modules are presented when applying the UP (Barlow and Farchione, 2017). Thus, in our study the intervention will consist of 8 online individual sessions with a 1 h duration conducted through Google Meet video-calls. As shown in Table 3, five specific psychological abilities (i.e., awareness of emotions, cognitive flexibility, emotion-driven behaviors, exposure to physical sensations and emotional expositions) will be distributed over 8 sessions.

**Table 3 tab3:** Sessions and contents of the Unified Protocol-based psychological intervention for patients with post COVID-19 condition.

Session title	Contents and exercises
1. Setting goals and maintaining motivation.	This session is focused on setting general goals to be developed during the intervention as well as the steps to achieve these goals. Exercise – decisional balance: a decisional schedule is worked out with the patient in order to analyse benefit/inconvenience of change and benefit/inconvenience of remaining unchanged. The aim of this exercise is to motivate the patient to move toward the change.
2. Understanding emotions.	In this session, patients learn about the adaptive function of emotions and how to analyse their emotional responses. Exercise – ARC: patients register their emotional responses (Antecedent - Response – Consequences). The aim of this exercise is that patients learn how to identify their emotional responses and how thoughts, physical sensations and behaviors are interrelated.
3. Mindful emotion awareness.	The third session aims to teach how to be in the present without judging the emotional experience. Exercise - Meditation: three different exercises of increasing difficult are proposed (guided meditation, emotion induction and anchoring themselves in the present). The objective of these exercises is for patients to observe their emotional responses in the present and without judgment.
4. Cognitive flexibility.	This session focuses on learning the relationship between thoughts and emotions, learning about automatic irrational thoughts and practicing the cognitive flexibility. Exercise – Cognitions: identification of thoughts and practicing cognitive flexibility. Exercise – Problem solving: identifying problematic situations and proposing rational alternatives. These exercises aim to observe thoughts and analyse whether they are describing the reality and help the patient to achieve their goals (if the patient reports an objective problem, problem-solving should be used) or whether they are irrational thoughts (patients should interpret them in a more flexible way, considering other possibilities).
5. Countering emotional behaviors.	During this session, patients learn the concept of emotionally-driven behaviors and the different kinds of avoidance behaviors. Exercise - Opposite behaviors: this exercise aims to help patients to identify avoidance behaviors and propose an alternative or opposite behavior.
6. Emotional expositions (I).	The sixth session aims to instruct patients on the relationship between body sensations and emotional responses, to encourage patients to face internal and external stimuli that cause distress and to learn how to tolerate them progressively. Exercise – Emotional expositions I: the objective of this exercise is for patients to identify physical unpleasant sensations that cause discomfort. Then, they will train their ability to tolerate them by doing exercises that simulate the body sensations they have identified (i.e., running may increase heart rate).
7. Emotional expositions (II).	In this session, participants continue with the exercises of the previous session through a hierarchy of exposition. Exercise – Emotional expositions II: the aim of this exercise is for patients to identify unpleasant intense emotions in order to design their own hierarchy of exposure to these emotions based on fear and avoidance indicators. The final objective is for patient to learn how to progressively tolerate their emotions.
8. Recognizing accomplishments and looking to the future.	The last session is focused on summarizing the techniques learned during the program and the progress in the management of emotions. Patients also identify future hard situations to propose an adaptive way to overcome them. Exercise – looking to the future: the aim of this exercise is to plan the abilities that need to be reinforced. Patients propose the techniques that will help them in possible difficult situations in the future and propose short-term and long-term objectives to maintain all the progress achieved during therapy.

All sessions will follow the same schedule. New concepts and abilities will be introduced at the beginning of each session. Then, participants will answer true/false questions to ensure they have understood the main ideas of the session and any doubts will be resolved. After the questions, participants will be instructed on how to do the exercises proposed and they will be encouraged to practice at home until the next session. Once the session has finished, participants will receive a manual by e-mail with the main information of the session, the exercises and the corresponding registers.

### Data analysis

2.6.

The Statistical Package for the Social Sciences (SPSS) version 22.0 for windows (IBM Corp, 2013) will be used to conduct the statistical analysis.

First, normal distribution test will be conducted to explore whether the data obtained followed a normal distribution. According to the distribution of the sample, we will use parametric or non-parametric analyses. Then, descriptive data (mean, standard deviation, and proportions) of all study variables will be reported in order to characterize the sample (i.e., sociodemographic and psychosocial status). Missing-value analysis and the Little Missing Completely At Random test (MCAR) will be used to check whether missing values are randomly presented. Last observation carried forward (LOCF) will be used in this case (Jakobsen et al., 2017).

Analysis of Variance (ANOVA), or its equivalent non-parametric Friedman test, will serve to test whether there are differences between the three baseline conditions at pre-assessment to ensure that randomization resulted in comparable groups. Repeated measures ANOVA will help to determine if between-group (differences in outcome variables between the three baseline conditions at different assessment points) and within group differences (differences between the pre-treatment and the remaining assessments in the outcome variables for each baseline condition) are present. Additionally, effect sizes (Cohen’s *d*) will be calculated for both between and within group analyses. Effect sizes will be interpreted as small (*d* ≈ 0.2), medium (*d* ≈ 0.5) or large (*d* ≈ 0.8).

As recommended for n-of-1 trials, visual analysis of the data by graphs will also be used to determine whether the psychological outcomes improve as a consequence of intervention contents. By doing so, we will establish the baseline pattern on OASIS and ODSIS scales and compare it with the data within the following treatment phase and also with results obtained during the follow-up assessments. The statistical Software R version 4.1.0 (R Core Team, 2021) will be used for the graphical representation of slopes.

Adherence to the intervention will be calculated (proportion of attendance to sessions compared with programed ones) as a measure of programs acceptability. With the same purpose, we will conduct qualitative analyses of reports provided in open questions regarding the satisfaction with the program. Content analysis will be performed with the MAXQDA program (Kuckartz and Rädiker, 2019).

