#### Sample size calculation

2.2.2.

In order to stablish the sample size required for this trial, we follow recommendations by Bell et al. (2018) which proposed that a sample size of 60 participants would be adequate considering an effect size of 0.3 and 80% of power. Following this recommendation, our sample will be comprised of 60 participants, 20 in each baseline condition (6, 8 and 10 days of assessment before the intervention).

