**Figure 1 fig1:**
[figure not shown]
Flow chart of participants and procedures.

Participants who meet the inclusion criteria (Table 1) will be given the information sheet and will sign the informed consent in the face-to-face consultation with the nursing team. Then, the psychologist of the study ([name]) will contact participants by telephone and will arrange an online session through a video-call to assess EDs according to the Anxiety and Related Disorders Interview Schedule for DSM-5 (ADIS-5; Brown and Barlow, 2014) which would also help to explore if any exclusion criteria are present (i.e., participants present a severe mental health issue or current suicidal ideation). Patients who meet any of these exclusion criteria will be recommended to consult with their mental health service of reference. If inclusion criteria are accomplished, participants will receive the pre-assessment protocol through e-mail and they will answer the questionnaires via the online platform Google Forms. Once the pre-assessment is completed, each participant will be sequentially and randomly assigned to one of the three multiple baseline conditions (Condition 1: 6 days of baseline assessments; Condition 2: 8 days of baseline assessments; Condition 3: 10 days of baseline assessments). During the baseline period, participants will receive daily e-mails with the online baseline assessment to be answered through Google Forms. Randomization to different baseline conditions will be conducted with a computer-generator online software (www.randomizer.org). An independent researched not involved in the implementation of the psychological intervention will sequentially assign participants to the three baseline conditions. Participants and professionals will know the baseline condition to which patients have been assigned.

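### Section 2.6 names the Friedman test, a related-samples test, for comparing three independent baseline conditions at pre-assessment; the rank test that fits is Kruskal-Wallis

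*Protocol article*

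**What the plan says.** Section 2.6 (Data analysis) begins with a normality test and lets the result choose the family of methods: "According to the distribution of the sample, we will use parametric or non-parametric analyses". It then names the test for the comparison at pre-assessment: "Analysis of Variance (ANOVA), or its equivalent non-parametric Friedman test, will serve to test whether there are differences between the three baseline conditions". The stated purpose is "to ensure that randomization resulted in comparable groups".

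The structure of the groups is given elsewhere. Section 2.3 (Procedures) says that, after pre-assessment, "each participant will be sequentially and randomly assigned to one of the three multiple baseline conditions". Section 2.2.2 (Sample size calculation) says "our sample will be comprised of 60 participants, 20 in each baseline condition".

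Change over time is handled in the next sentence of section 2.6, by a different method: "Repeated measures ANOVA will help to determine if between-group" and within-group differences are present. That sentence names no rank-based counterpart.

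**The concern.** Friedman's test is for the same person, or the same matched block, measured under each of k conditions. It is not the rank counterpart of a one-way ANOVA on separate groups; Kruskal-Wallis is. The plan calls Friedman the equivalent of ANOVA and assigns it to a comparison between separately randomised patients at a single time point.

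If normality is rejected, the analyst has two courses. One is to find that the prespecified test cannot be run and to substitute another without any basis in the plan. The other is to line up unrelated patients as if they were matched and report a p-value that a different sort order would change. At stake is a comparability check that another analyst could not reproduce.

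**Working it through.** **Inputs from the protocol article.** Three conditions (section 2.1); 20 participants in each, 60 in total (section 2.2.2); each participant in one condition only (section 2.3); one time point, pre-assessment (section 2.6). No pairing, matching or blocking across conditions is described. The plan gives no figure for this test, so there is none to reproduce.

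**Reading the sentence.** Could Friedman have been meant for change over time? The sentence fixes both the contrast (between conditions) and the time point (pre-assessment), and states a randomisation check as its purpose. The longitudinal analysis follows separately. The wording therefore assigns Friedman to independent groups.

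**What each statistic uses** (without tie correction).

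- Friedman, n rows and k columns, with R_j the sum of within-row ranks in column j: Q = 12/[n k (k+1)] x sum(R_j^2) - 3n(k+1). With n = 20 and k = 3, 12/240 = 0.05 and 3 x 20 x 4 = 240, so Q = 0.05 x sum(R_j^2) - 240. The R_j depend on which three patients share a row, and the design does not define that.
- Kruskal-Wallis, N patients, with R_j the sum of pooled ranks in group j: H = 12/[N(N+1)] x sum(R_j^2/n_j) - 3(N+1). With N = 60, 12/(60 x 61) = 12/3660 and 3 x 61 = 183. No row enters the formula, so order cannot matter, and the n_j may differ.

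**Can Friedman be computed?** With one row per participant and one column per condition, every row has one value and two blanks, so no complete row exists. With group sizes of 19, 20 and 21 (an example; the plan is 20 each), the routine stopped with an error.

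**How far the p-value moves with row order.** The simulation assumed integer scores from 0 to 20, mean 10 and SD 3.5 in the lowest group, and 20 per group. These values are not from the document. Each fixed data set was re-ordered 5,000 times within groups for Friedman, and the first 200 orderings were checked for Kruskal-Wallis.

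| Built-in spread, extreme groups | Kruskal-Wallis p | Friedman p, min to max | Friedman p, central 95% | Orderings with Friedman p < 0.05 |
|---|---|---|---|---|
| 0 | 0.7726 | 0.09 to 1.00 | 0.26 to 0.99 | 0% |
| 2 points | 0.89 | 0.08 to 1.00 | 0.31 to 0.99 | 0% |
| 3.5 points (1 SD) | 0.0253 | 0.0005 to 0.67 | 0.004 to 0.25 | 54% |

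Kruskal-Wallis gave a single p-value in every ordering checked. In the third data set one-way ANOVA gave 0.0158.

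**Type I error over random orderings** (nominal 5%, assumed two-sided). In 5,000 simulated trials of the same kind, Friedman rejected in 4.5% and Kruskal-Wallis in 4.7%. In a separate run of 6,000 trials with normal data, the rates were 5.0% and 4.8%. Friedman is thus near nominal on average. The fault is arbitrariness and non-computability, not excess false positives.

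**The case against.** The strongest case on the other side is that little depends on this sentence. Randomisation follows completion of the pre-assessment (section 2.3), so any pre-assessment difference between conditions is due to chance. Section 2.6 ties no adjustment, exclusion or other decision to the result. Everyone receives the same intervention (Discussion), the study is described as a pilot (section 2.1), and the hypotheses concern pre-to-post change and its maintenance (Introduction). All of this stands, and it sets the severity. An analyst with an ordinary file would also probably notice that the test does not run. That stands too, but it confirms that the named test is the wrong one.

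Four stronger readings are tempting, and the document does not support them.

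- *The non-parametric branch leaves the longitudinal or between-condition analysis without a valid test.* Section 2.6 assigns repeated measures ANOVA there, not Friedman. At most a rank counterpart is unnamed, which a condensed article may leave to the full plan.
- *The comparability check loses important power.* The simulations do show lower power for Friedman (54% against 66% with shifts of 0, 0.45 and 0.9 SD; 67% against 77% with a 1 SD spread). Those figures presuppose true differences before randomisation, which random assignment rules out.
- *The fallback will probably be used because eligibility truncates the scores.* Table 1 admits patients on either scale, or on an ADIS-5 diagnosis alone, so neither score is simply cut off. How often normality will be rejected cannot be judged from the document.
- *A mixed model should replace the whole approach.* That is a separate design preference, which correcting a wrong test name does not require.

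**Conclusion.** The point holds as an error in stated text: a related-samples test is assigned to three independent groups. It rests on the plain wording of section 2.6 and on the absence of any described matching, not on the simulated scores. The simulation only illustrates the consequence, and its size depends on the assumed data: of the three data sets, only the one with a 1 SD spread gave Friedman p-values on both sides of 0.05.

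The reach is narrow. It covers one comparability check, at one time point, and only if normality is rejected. Average type I error remains near 5%, and inference on pre-to-post change is not directly affected. Severity: minor.

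**What to change.** In section 2.6, replace Friedman with Kruskal-Wallis for the comparison of the three conditions at pre-assessment. For example: *one-way ANOVA, or the Kruskal-Wallis test where a non-parametric method is used, will compare the three baseline conditions at pre-assessment.* If the authors want Friedman in the plan, it should be tied explicitly to comparisons across assessment points within the same participants.

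The cost is one sentence. No data, procedure, sample size or patient is affected. Section 2.6 already uses SPSS, and Kruskal-Wallis is a standard test that works on the one-row-per-participant file and on unequal groups.

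### The pre-assessment significance test cannot show that the three baseline conditions are comparable; adjusting the between-condition comparisons for the pre-score would handle chance imbalance

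*Protocol article*

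**What the plan says.** Section 2.3 (Procedures) fixes the order of events: "Once the pre-assessment is completed, each participant will be sequentially and randomly assigned to one of the three multiple baseline conditions". Section 2.2.2 sets the group size: "our sample will be comprised of 60 participants, 20 in each baseline condition".

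Section 2.6 (Data analysis) then plans two steps.

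- **Check at pre-assessment.** "Analysis of Variance (ANOVA), or its equivalent non-parametric Friedman test" will be used "to test whether there are differences between the three baseline conditions at pre-assessment to ensure that randomization resulted in comparable groups". No action is attached to a significant result.
- **Outcome model.** "Repeated measures ANOVA will help to determine if between-group (differences in outcome variables between the three baseline conditions at different assessment points"), together with within-group "differences between the pre-treatment and the remaining assessments in the outcome variables for each baseline condition". Cohen's d is planned for both kinds of comparison. No covariate is named; the pre-score appears as one of the repeated assessments and as the reference for change.

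**The concern.** The plan gives the test a purpose it cannot serve. Pre-scores are recorded before allocation, so allocation cannot influence them. If allocation is sound, the null hypothesis is true by design, and the test only reports whether chance produced an unusual draw. Non-significance then says little about how far apart the three means are, because with 20 per condition quite large gaps stay above p = 0.05.

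At stake is the reading of the planned between-condition results. If the test is non-significant and the groups are declared comparable, a chance imbalance in OASIS or ODSIS can go unremarked. It can then enter the comparison of conditions at post and follow-up and the Cohen's d reported beside it. The model named in section 2.6 does not remove it.

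**Working it through.** The plan states no error rate or power for this test, so there is no figure of its own to reproduce. The effect size of 0.3 and the 80% power in section 2.2.2 are not tied to this test and are not used here.

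**Inputs**
- 3 conditions, 20 participants each (section 2.2.2).
- Pre-assessment before randomisation (section 2.3).
- Significance level 0.05, two-sided: assumed; the article does not state it.
- Pre-post correlation r: not given; assumed 0.3, 0.5 and 0.7, with equal SD at pre and post.

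**Step 1. How often chance alone produces a visible gap.** Each condition mean has standard error 1/√20 = 0.224 SD. A gap of 0.5 SD between the highest and lowest of three means is 0.5 × √20 = 2.24 standard errors. The range of three normal means reaches this with probability 0.254. If the gap is scaled by the SD estimated from the trial, a simulation of 100,000 randomisations gives 0.263. Either way it is about one trial in four for one scale. The ANOVA rejects in about 5% of the same trials (0.051 simulated).

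**Step 2. What a non-significant result leaves open.** In that simulation, 22% of non-significant results still had a spread of at least 0.5 SD, and 59% a spread of at least 0.3 SD. Turned round, 0.223 × (1 - 0.051) / 0.263 = 0.80, so about 80% of the imbalances of 0.5 SD or more pass the test. The limit follows directly. With the middle mean halfway, the means are -D/2, 0 and D/2, and their variance is D²/4, so F = 20 × D²/4 = 5D². The 5% critical value of F on 2 and 57 degrees of freedom is 3.16, so D = √(3.16/5) = 0.79. Means up to 0.79 SD apart can therefore be non-significant. Section 2.6 itself treats about 0.8 as a large effect.

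**Step 3. What a 0.5 SD pre imbalance does to a between-condition comparison with no true difference.** Comparing post scores, the expected shift is 0.5 × r. Comparing change from pre, it is 0.5 × (r - 1).

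| r | Shift, post scores | Shift, change scores |
|---|---|---|
| 0.3 | +0.15 SD | -0.35 SD |
| 0.5 | +0.25 SD | -0.25 SD |
| 0.7 | +0.35 SD | -0.15 SD |

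Unadjusted post scores under-correct and change scores over-correct. Using the pre-score as a covariate removes the shift in expectation.

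**Step 4. Precision.** Relative to a post-score variance of 1, the variance of a change score is 2(1 - r), and the residual variance after covariate adjustment is 1 - r².

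| r | Post | Change | Adjusted | Cut against post | Cut against change |
|---|---|---|---|---|---|
| 0.3 | 1 | 1.40 | 0.91 | 9% | 1 - 0.91/1.40 = 35% |
| 0.5 | 1 | 1.00 | 0.75 | 25% | 25% |
| 0.7 | 1 | 0.60 | 0.51 | 49% | 1 - 0.51/0.60 = 15% |

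These figures describe a comparison at one post-treatment occasion. They are a guide to the repeated-occasion analysis, not an exact result for it.

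**The case against.** **No main conclusion is touched.** The hypotheses at the end of the Introduction concern improvement from pre to post and its maintenance. Section 2.1 makes each participant their own control, and the Discussion states that all conditions receive the same intervention. A reader might infer that an imbalance between conditions would bias the trial's main result. The documents do not support that. This objection stands in full and limits the point to the between-condition comparisons.

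**The pre-score is already in the model.** A reader might infer that it is ignored. It is not: as a level of the repeated factor it makes the condition-by-time term a comparison of change from pre. But change scores over-correct a chance imbalance, and a condition effect averaged over occasions carries it forward. This objection narrows the point without removing it.

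**A condensed article may leave covariates to a full analysis plan.** That is fair, and the absence of a covariate is not counted as an omission. The stated purpose of the test is in the text, however, and the covariate is an improvement on the model the text names.

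**The check may still have a use.** Assignment is sequential and the condition is known to professionals, so a marked pre-assessment difference could prompt a look at the allocation process. This has limited force: it is a different purpose from showing comparability.

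**Two stronger figures are tempting and should not be used.** Treating 15 pre-assessment scores as independent gives a 54% chance of at least one false alarm (1 - 0.95^15). But the article does not say which variables are tested, the scales overlap, and positive correlation would lower the figure; nor does a significant result trigger any action. The test's power of 26% to 34% against a 0.5 SD spread presumes a true difference, which sound randomisation rules out.

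**Conclusion.** The point holds in limited form. Section 2.6 assigns the pre-assessment test a task that it cannot perform at any sample size. With 20 per condition a spread of at least 0.5 SD arises by chance in about 25% of trials per scale, against about 5% flagged. This rests on sound allocation, approximate normality and a 5% level. The consequence for a between-condition comparison is a shift of 0.15 to 0.35 SD in size per 0.5 SD of imbalance, in opposite directions for post and change scores; this rests on the assumed correlation range of 0.3 to 0.7. It is a minor, worthwhile correction to a secondary analysis.

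**What to change.** In section 2.6, or in the analysis plan:

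- Report pre-assessment scores by baseline condition descriptively, and do not use a significance test as evidence that the conditions are comparable.
- In each between-condition comparison at post and follow-up, include that outcome's pre-assessment score as a covariate (ANCOVA or mixed model), whatever balance is observed, and derive the between-condition effect size from the adjusted comparison.
- Leave the within-person pre-to-post analyses as they are.

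Every outcome scale that Table 2 schedules at post and follow-up is also collected at pre-assessment, so no new data are needed. The cost is a change of wording and slightly more analysis work.
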